**What is already known on this subject? AND**

**What does this study add?**

Peri-operative pain management in pediatric surgeries is considered a challenging issue for the anesthesiologists. The usage of regional anesthesia in association with general anesthesia (GA) is a simple intraoperative way that reduces (GA) requirements and side effects. Recently, paraspinal fascial plane block, the sacral multifidus plane block (MPB), was used successfully in infants. The study has been designed to determine the effect of MPB versus caudal epidural block to control peri-operative pain in hypospadias surgeries in children.

## **1. INTRODUCTION/ REVIEW**

Hypospadias is the second most common birth defect in boys after cryptorchidism. It is characterized by incomplete development of the urethral fold and the ventral foreskin of the penis that causes abnormal positioning of the urethral opening that needs surgical intervention under general anesthesia. **(Donaire and Mendez, 2023)**

The hypospadias surgery is known to be associated with acute severe pain and requires potent analgesia post-surgical for long term, Despite the prodigious advance in the knowledge of mechanisms of acute post-operative pain, The effective and safe analgesic methods is still under research especially for children. **(Elbadry *et al.*, 2023)**

Since opioids are associated with respiratory depression, severe sedation, disorientation, constipation and urinary retention, there is high incidence of opiophobia with consequent inappropriate dosage prescription, particularly in the pediatric population. **(Mahajan *et al.*, 2021)**

Regional anesthesia is the infiltration of a peripheral nerve with an anesthetic agent and blocking transmission to avoid or relieve perioperative pain. Regional anesthesia can be used in coincidence with general anesthesia, postprocedural, and often for many acute and chronic pain conditions. **(Folino and Mahboobi, 2023)**

A variety of peripheral and central nerve blocks have been developed as a regional anesthesia in children to ensure that perioperative pain can be effectively controlled in a safe way, chief among them is single-injection caudal block, The first author to describe caudal anesthesia for children was Meredith Campbell in 1933. **(Campbell, 1933; Wiegele, Marhofer and Lönnqvist, 2019)**

Caudal blocks have been proved to be effective for perioperative analgesia for painful sub-umbilical surgeries, it is safe, simple, and has a high success rate. However, the main disadvantage is its limited duration of action. **(Hassan, Hassan and Elmetwally, 2018)**

The erector spinae plane block (ESPB) is a new paraspinal plane block first described in 2016 to relieve thoracic pain, then described for the first time for sacral dermatomes for a pilonidal sinus surgery by Tulgar et al. in 2019. (Forero *et al.*, 2016; Tulgar *et al.*, 2019)

Recently, a paraspinal fascial plane block, the sacral multifidus plane block (SMPB), has been reportedly used successfully in infants. SMPB is technically similar but anatomically different from ESPB where two separate injections of local anesthetic occur which targets the fascial plane underneath sacral multifidus muscle just laterally to the midline. (Sacral Multifidus Plane/Sacral ESP Block — **BABY BLOCKS**, no date)

The possible mechanism of action of SMPB includes blocking the dorsal rami and medial cluneal nerves directly by local anesthetic (LA) deposition and ventral rami by anterior LA spread through dorsal and ventral sacral foramina. The SMPB may also block the pudendal nerve (S2–S4), lumbosacral plexus, and sciatic nerve via the anterior and cranial LA spread. (Mistry *et al.*, 2022)

Aksu and Gurkan first describe the longitudinal midline approach and its ability to provide effective analgesia for an infant undergoing hypospadias repair, and additionally hypothesized that epidural spread may occur, though the mechanism of this is not well elucidated. (Aksu and Gürkan, 2020)

The sacral multifidus plane block is considered a promising block in neonates for peri-operative analgesia. However, no data exists comparing caudal and sacral multifidus plane blocks in pediatric populations. (Mahajan *et al.*, 2021)

## 2. AIM/ OBJECTIVES

This study aims to evaluate the safety and efficacy of ultrasound-guided sacral multifidus plane block and compare its analgesic effect to ultrasound-guided caudal block in pediatric patients undergoing hypospadias surgery under general anesthesia. The primary outcome of the study is to compare the time for the first time to rescue analgesia postoperatively in the two groups. The secondary outcome is to compare the two blocks as regard; hemodynamic parameters, the total intraoperative IV fentanyl requirements, postoperative FLACC pain score and complications.

## 3. METHODOLOGY:

### Patients and Methods

- Type of Study: Randomized controlled clinical trial.
- Study Setting: Ain-shams University Hospitals, Cairo, Egypt.
- Study Period: 6 months -1 year from approval of ethical committee.
- Study Population: Pediatric patients undergoing Hypospadias surgery.
- Sample size: By using Power Analysis and Sample Size (PASS 15)(Version 15.0.10) for sample size calculation, setting power at 99%, alpha error 0.05 and after reviewing previous study results (Ozen and Yigit, 2020) showing that among Pediatric Patients underwent hypospadias surgery, the median time of first rescue analgesics was lower in those took caudal epidural block than those took ultrasound-guided dorsal penile nerve block (14[12-17] versus 20.50 [20-21]respectively); Based on that and after considering 20% dropout rate, a sample size of at least 30 pediatric patients undergoing hypospadias surgery divided randomly into 2 groups (15 patients in each group) and will be sufficient to achieve study objective.

**Inclusion Criteria:**

- Children aged (1 –7) years old.
- All patients will be of ASA classification I, II physical status.

**Exclusion Criteria:**

- Parents refusing to participate are excluded from the trial.
- Children who had spinal anomalies, altered mental status.
- A history of developmental delay.
- Blood diseases: Coagulopathy or anaemia.
- Infection at the site of injection.
- Drug allergy.

**Sampling Method:**

Computer generated random number lists.

• **Ethical Considerations:**

The procedure will be done under supervision of the main supervisor and by an expert. The study will be performed after approval of the Research Ethical Committee of the Faculty of Medicine, Ain Shams University and informed written consent from the parents. The study protocol will be explained to the parents (care givers) before taking their consent to participate in the study and the type of anaesthesia and surgical procedure.

• **Study Procedures:**

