**1-Pre-operative settings:**

Detailed preoperative history will be taken from the parents of the child for any medical disorder, physical examination and preoperative investigations (complete blood picture, Bleeding Time, prothrombin time and partial

thromboplastin time) will be performed. Age and weight will be recorded. The patient will be fasting according to guidelines preoperatively.

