## 2-Intra-operative Settings

Inside the operating room, mean arterial blood pressure (MAP), heart rate (HR), electrocardiography (ECG) and peripheral oxygen saturation (SpO2) will be obtained using standard non-invasive monitors and base line values will be recorded.

General anesthesia will be induced using face mask with sevoflurane (4-8%) in 80% oxygen, then an intravenous (IV) cannula will be secured. Patients aged (1-4) years an One µg/kg fentanyl will be given and intubation will be facilitated by 0.5 mg/kg atracurium, While Patients aged 4-6 years will receive fentanyl 1 µg/kg, propofol 1-2 mg/kg and intubation will be facilitated by 0.5 mg/kg atracurium. Isoflurane 1%-2% with oxygen was used for anaesthetic maintenance. After stabilizing the patient's hemodynamics and before skin incision, the blocks will be done. (Ozen and Yigit, 2020)

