## Groups:

The eligible patients will be enrolled in this double blinded study and randomly allocated into one of two parallel equal groups (15 patients in each group) according to sample size by computer generated random number lists. The allocation will be concealed using closed opaque envelopes. Both the patient and the investigator who collected the data after the block will be blind to the study group.

- Multifidus plane block (MPB) group(n=15): Participants will receive injection volume of 1 ml.kg of 0.25% bupivacaine at the fascial plane between the multifidus muscle and the median sacral crests of S2 and S3. (**Suresh *et al.*, 2018; Mahajan *et al.*, 2021**)
- Caudal block (CB) group (n=15): Participants will receive 1 ml.kg of 0.25% bupivacaine, between the two sacral cornua. (**Campbell, 1933; Suresh *et al.*, 2018**)

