#### 2-Analytical statistics:

- Independent-samples t-test of significance was used when comparing between two means.
- Chi-square (X) test of significance was used in order to compare proportions between two qualitative parameters.
- Mann Whitney U test: for two-group comparisons in non-parametric data.
- The confidence interval was set to 95% and the margin of error accepted was set to 5%. So, the p-value was considered significant as the followings:

- Probability (P-value):

P-value  $<0.05$  was considered significant.

P-value  $<0.001$  was considered as highly significant.

P-value  $>0.05$  was considered non\_significant.

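### Children aged 1-7 years are compared with unadjusted two-group tests although age is recorded and changes induction; adjust for age, and compare fentanyl per kg

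*Protocol*

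**What the plan says.** - **Eligibility** (Protocol, Inclusion Criteria): "Children aged (1 –7) years old".
- **Induction by age** (Protocol, 2-Intra-operative Settings): for the younger band, "Patients aged (1-4) years an One µg/kg fentanyl will be given", with atracurium. For the older band, "Patients aged 4-6 years will receive fentanyl" at the same dose per kg, the same atracurium and, in addition, propofol. The bands are written as 1-4 and 4-6 years.
- **Allocation** (Protocol, Sampling Method and Groups): "Computer generated random number lists", two equal groups of 15, and "The allocation will be concealed using closed opaque envelopes". No stratification factor is named.
- **Data collected** (Protocol, 1-Pre-operative settings): "Age and weight will be recorded". No stated allocation or analysis step uses either variable.
- **Tests** (Protocol, 2-Analytical statistics): "Independent-samples t-test of significance was used when comparing between two means", Mann-Whitney U for non-parametric data and chi-square for proportions. None carries a covariate.
- **Outcomes** (Protocol, Measurements and 3- Post-operative settings): the primary outcome is time from recovery to first rescue, triggered by FLACC of 3 or more. Secondary outcomes include total intraoperative fentanyl in µg, heart rate and mean arterial pressure, FLACC, and complications.

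**The concern.** Several outcomes can be expected to vary with age or size over this range, and the stated tests leave that variation in the error term.

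- **Fentanyl** is given per kg at induction but compared as a total in µg. An arm with heavier children therefore tends to show a higher total whatever the block does.
- **Heart rate and mean arterial pressure** are compared as absolute values across ages 1 to 7. That they change with age is ordinary physiology; the protocol gives no figure for it.
- **FLACC**, which triggers the primary event, is described in the protocol as a scale for children who cannot yet report their own pain. Eligibility nevertheless runs to 7 years, so the scale may behave differently across the range.
- **Induction** differs by age, so an age imbalance is also an imbalance in who received propofol.

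Two things are at stake with 15 per arm. One is precision. The other is how far the single allocation obtained can be trusted if it happens to be unbalanced on age.

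**Working it through.** **1. The plan's own sample size.** Inputs (Protocol, Sample size): medians 14 and 20.5, so the difference is 6.5 h; caudal bracket 12-17; power 99%; alpha 0.05; dropout 20%. Assumptions: the bracket is an interquartile range, the test is two-sided, and the caudal spread applies to both arms.

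- SD = (17 − 12)/1.349 = 3.71 h
- n = 2 × (1.960 + 2.326)² × (3.71/6.5)² = 11.9, rounded up to 12 per arm
- 12/(1 − 0.20) = 15 per arm, 30 in total

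The stated 30 is reproduced. Age plays no part in it.

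**2. How often the arms differ on age.** With 15 per arm fixed and K of 30 children in the older band, the number of older children in one arm is hypergeometric. K is an assumption.

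| K older of 30 | P(difference ≥ 3) | P(difference ≥ 4) | P(difference ≥ 5) |
|---|---|---|---|
| 6 | 17% | 17% | 1.7% |
| 9 | 43% | 11% | 11% |
| 12 | 26% | 26% | 6% |
| 15 | 47% | 14% | 14% |

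For K = 12, a difference of 4 or more means a split of 8 to 4 or worse. P = 1 − P(5, 6 or 7 in one arm) = 1 − 0.736 = 0.264.

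**3. Shift in the primary time.** Shift = (imbalance/15) × age-band effect. The protocol gives no age effect, so this is a range by assumption.

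- Effect 0 h: shift 0
- Effect 2 h: 4/15 × 2 = 0.53 h, or 8% of 6.5 h
- Effect 4 h: 4/15 × 4 = 1.07 h, or 16% of 6.5 h

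On the SD in step 1, 2-4 h is about 0.5-1.1 SD, so the upper end is a large age effect.

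**4. What this does to the test.** Simulation with 15 of 30 children older; the age effect is in SD units within an age band.

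- Type I error of the unadjusted t-test over all allocations: 0.05, whatever the age effect.
- Given a difference of 5 or more older children: about 0.07, 0.12 and 0.17 for age effects of 0.5, 1.0 and 1.5 SD. With age in the model it is 0.05 to 0.06.
- Power for a 1 SD block effect with a 1 SD age effect: 0.65 unadjusted, 0.74 adjusted. With no age effect: 0.75 unadjusted, 0.74 adjusted.

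**5. Net gain from adjusting.** The large-sample gain is 1/(1 − r²), with r the assumed correlation of age with outcome. Estimating one covariate with 30 children inflates the variance by about 1 + 1/26 = 1.038.

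- r = 0.3: 1.099/1.038 = 1.06
- r = 0.5: 1.333/1.038 = 1.28
- r = 0: 1/1.038 = 0.96

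**6. Fentanyl.** At 1 µg/kg at induction, each kg of difference in mean weight between arms moves the difference in mean totals by 1 µg from that dose alone, if the induction dose is counted in the total. Division by weight removes this term.

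**The case against.** The strongest reply is that the plan contains no error here. Concealed allocation from a computer-generated list into two equal groups is a valid design. Chance imbalance is already part of the error that the t-test and Mann-Whitney test allow for, and type I error stays at 0.05 over all allocations. This stands. A reader might infer that the absence of an age stratum confounds the trial or invalidates the unadjusted tests; the documents do not support that. What remains is lost precision, and distortion conditional on the allocation obtained.

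The size of the harm also rests on assumptions, since the protocol gives no age distribution and no age effect on rescue time. That stands too. The bands differ only in propofol, given before the block, while the primary clock starts at recovery. No section links that propofol to rescue hours later. A serious distortion of the primary outcome therefore cannot be asserted. On the other side, the 6.5 h comes from caudal versus dorsal penile nerve block, and the Introduction says no data compare the two blocks studied here. A smaller true difference would give a shift of 0.5-1.1 h more weight.

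A further reply is that adjustment is often left to an SAP, which is not at hand. The fair answer is limited: the protocol does name its comparative tests, and they are unadjusted. If an SAP already adjusts for age, the two documents need only be aligned.

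Finally, a reader might conclude that allocation must be stratified by age. The bands as written overlap at 4 years and stop at 6, while eligibility runs to 7, so they cannot yet define strata. Varied block sizes in two strata of so small a trial could also move the arms away from 15:15 by more than one or two.

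**Conclusion.** The point holds as one of efficiency and robustness, not of validity. The protocol records age and weight, enrols over a range in which its own induction changes, and names only tests that ignore both variables. An imbalance of 4 or more older children has an 11-26% chance over the assumed shares of 6 to 15 older children in 30 (26% at 12).

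The case is clearest for total fentanyl in µg and for heart rate and mean arterial pressure. For the primary time it is modest: about 0.5-1.1 h against a planned 6.5 h, and only if the age bands differ by 2-4 h, which is assumed. Adjustment is worth about 6-28% in effective sample size at assumed correlations of 0.3-0.5, and costs about 4% if age is unrelated to outcome.

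**What to change.** 1. Prespecify recorded age, as a continuous covariate, in the primary comparison and in the FLACC and hemodynamic comparisons. Where normality fails, a rank-based analysis of covariance keeps the protocol's non-parametric route. Report the unadjusted test as a supporting analysis.
2. Compare intraoperative fentanyl per kg using recorded weight, and state whether the induction dose is counted.
3. Reconcile the age range in Inclusion Criteria with the bands in 2-Intra-operative Settings (overlap at 4 years, no band above 6). Which reading applies is for the investigators to settle.
4. Optionally, and only if enrolment has not begun and item 3 is done, stratify allocation by age band with small fixed blocks and separate envelope sets.

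Items 1 and 2 need no extra patients and no new data, only a protocol or SAP edit made before unblinding. Their cost is the loss of about 4% if age proves irrelevant. Item 4 needs a second list and envelope set, and arm sizes may still differ slightly from 15:15.

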**1-Pre-operative settings:**

Detailed preoperative history will be taken from the parents of the child for any medical disorder, physical examination and preoperative investigations (complete blood picture, Bleeding Time, prothrombin time and partial

thromboplastin time) will be performed. Age and weight will be recorded. The patient will be fasting according to guidelines preoperatively.

## 2-Intra-operative Settings

Inside the operating room, mean arterial blood pressure (MAP), heart rate (HR), electrocardiography (ECG) and peripheral oxygen saturation (SpO2) will be obtained using standard non-invasive monitors and base line values will be recorded.

General anesthesia will be induced using face mask with sevoflurane (4-8%) in 80% oxygen, then an intravenous (IV) cannula will be secured. Patients aged (1-4) years an One µg/kg fentanyl will be given and intubation will be facilitated by 0.5 mg/kg atracurium, While Patients aged 4-6 years will receive fentanyl 1 µg/kg, propofol 1-2 mg/kg and intubation will be facilitated by 0.5 mg/kg atracurium. Isoflurane 1%-2% with oxygen was used for anaesthetic maintenance. After stabilizing the patient's hemodynamics and before skin incision, the blocks will be done. (Ozen and Yigit, 2020)

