### -CB group

- In the left lateral position, CB will be done.

- The ultrasound transducer was first placed transversely at the midline to obtain the transverse view of sacral hiatus. At this level, the ultrasound transducer is rotated 90 degrees to obtain the longitudinal view of sacral hiatus. The block needle is inserted using the “in-plane” technique.
- After completing the block injection, the patient will be immediately placed in the supine position, IV Ringer’s solution 10 ml/kg/hour will be administered throughout the surgery.

Potential complications of the blocks:

- 1- Haemodynamic/systemic or local adverse events. Examples include arrhythmia, hypotension when combined with general anaesthesia.
- 2- Systemic toxic events from local anaesthetics may involve cardio- or neurotoxicity. Current guidelines recommend that any haemodynamic deterioration should be treated by Intralipid 20% as first-line therapy
- 3- Toxicity-related seizures that need to be treated with propofol, benzodiazepines, or barbiturates.
- 4- Infection/inflammation of the puncture site, sacral osteomyelitis, or local nerve injury which can be avoided by good sterilization before the block.
- 5- Inability to place the block and block failure, so children are generally sedated to ensure immobility during the puncture.
- 6- Local nerve injury, During MPB care must be taken not to inject directly into the posterior sacral foraminal, which lie lateral to the intermediate sacral crests.

Measurements:

The primary outcome of the study is to use the first time to rescue analgesia postoperative analgesic after two different block techniques to compare the analgesic effect.

The secondary outcome is to compare the two methods for;

- Hemodynamic parameters.
- The total intraoperative IV fentanyl requirements in µg.
- postoperative FLACC pain score and complications.

-Intraoperative:

- Hemodynamic parameters (heart rate and mean arterial pressure) and SpO2 will be measured and recorded just after performing the block and at 15 min interval till the end of the surgery.
- The total intraoperative IV fentanyl requirements in µg, anesthesia time in minutes (from induction of anesthesia till awake extubation), and surgical time in minutes (from skin incision until skin closure) will be recorded.

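### No heart rate or MAP is recorded between induction and block, so each block's own haemodynamic effect is mixed with that of anaesthesia and the comparison loses precision

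*Protocol*

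**What the plan says.** The order of events has to be put together from two places in the Protocol.

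- **Baseline.** Section 2-Intra-operative Settings opens in the operating room: MAP, heart rate, ECG and SpO2 "will be obtained using standard non-invasive monitors and base line values will be recorded".
- **Induction.** The next paragraph begins "General anesthesia will be induced using face mask with sevoflurane (4-8%) in 80% oxygen, then an intravenous (IV) cannula will be secured". Fentanyl and atracurium follow (with propofol in the older age band only), then intubation and isoflurane.
- **Block.** The same paragraph ends "After stabilizing the patient's hemodynamics and before skin incision, the blocks will be done". It does not ask for any value to be written down at that point.
- **Next reading.** The intraoperative part of the Measurements list (printed under the CB group heading) says heart rate, MAP and SpO2 "will be measured and recorded just after performing the block and at 15 min interval till the end of the surgery".

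On use of the data, section 2 (Aim/Objectives) states: "The secondary outcome is to compare the two blocks as regard; hemodynamic parameters". Children are "randomly allocated into one of two parallel equal groups (15 patients in each group"). For numerical data, section 2-Analytical statistics gives two-group tests: "Independent-samples t-test of significance was used when comparing between two means", or Mann-Whitney where data are non-parametric. It mentions no change from baseline.

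**The concern.** The only value labelled as baseline precedes the whole anaesthetic, and the next recorded value follows the block. Any change between the two carries induction, maintenance, positioning and block together. The protocol requires stable haemodynamics before the block, so the value that would separate induction from block is on the monitor at the time. It is simply not recorded.

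This matters in three ways.

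- Section 2 sets out to evaluate the safety of the multifidus plane block as well as to compare it with caudal block. If both blocks lowered MAP equally, the group difference would be zero and the data could not show the common fall.
- The list of potential complications names hypotension in combination with general anaesthesia. Randomisation balances groups in expectation; it does not say what happened to one child.
- A reading under anaesthesia is likely to predict the post-block value better than one taken before induction, so leaving it out costs precision.

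A later analysis plan cannot recover a reading that was never taken.

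**Working it through.** **Inputs.** From the Protocol: 15 per arm, two-group comparison, and the reading schedule above. Not in the Protocol and therefore assumed: correlation of the post-block value with the pre-induction value, r = 0.25 (range 0.2 to 0.3), and with a pre-block value under stable anaesthesia, r = 0.65 (range 0.6 to 0.7). Equal SDs at each time are also assumed. The Protocol states no haemodynamic figure to reproduce. Its one sample-size calculation ("setting power at 99%, alpha error 0.05") is for time to first rescue analgesia and is not an input here.

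**Step 1: what is mixed and what cancels.** Write the post-block value as pre-induction value + A + B, where A is the shift due to anaesthesia (same plan in both arms) and B is the effect of the block.

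- Within-arm change from the recorded baseline = A + B.
- Between-arm difference = (A + B1) − (A + B2) = B1 − B2.

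Illustration with assumed values A = −15, B = −3 and −8 mmHg:

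- Within-arm changes are −15 − 3 = −18 and −15 − 8 = −23, so the blocks' own effects cannot be read off.
- The between-arm difference is −18 − (−23) = 5, the true value. In 20,000 simulated trials of 15 per arm it averaged 4.97 from post-block values, 4.99 as change from the pre-induction baseline, and 4.99 as change from a pre-block reading.

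The missing reading therefore does not bias the comparison of the blocks.

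**Step 2: precision of the between-arm difference**, in units of the SD of the post-block value. Unadjusted SE = √(2/15) = 0.365. Adjusting for a baseline with correlation r multiplies this by √(1 − r²).

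| Analysis | Factor | SE (SD units) | Over the assumed range |
|---|---|---|---|
| Post-block value, unadjusted | 1 | 0.37 | – |
| Adjusted for existing baseline, r = 0.25 | √(1 − 0.0625) = 0.968 | 0.35 | 0.36 to 0.35 (r 0.2 to 0.3) |
| Adjusted for pre-block reading, r = 0.65 | √(1 − 0.4225) = 0.760 | 0.28 | 0.29 to 0.26 (r 0.6 to 0.7) |
| Change from pre-block reading, r = 0.65 | √(2(1 − 0.65)) = 0.837 | 0.31 | 0.33 to 0.28 (r 0.6 to 0.7) |

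The small cost of estimating a slope is ignored. It applies to both adjusted analyses, and it would use up part of the already small gain from 0.37 to 0.35.

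**Step 3: the same gain in children.** At r = 0.65, 15 per arm with adjustment for a pre-block reading is worth 15/0.5775 = 26 per arm unadjusted. Against adjustment for the existing baseline it is worth 15 × 0.9375/0.5775 = 24 per arm.

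**Note on the simulation.** Its SE fell from about 3.3 to 1.5 mmHg when the pre-block reading was used. The values chosen there imply a pre-block correlation of √65/9 = 0.90 (variance 65 before the block, 65 + 16 = 81 after it), well above the range in Step 2. It shows the direction; the table is the better guide to size.

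**The case against.** The strongest reply is that the stated outcome compares two randomised blocks under one anaesthetic plan, so the effect of anaesthesia cancels and nothing is wrong with the comparison. That stands. A reader might infer that the haemodynamic comparison is confounded by general anaesthesia, or that propofol in the older band biases it. The documents do not support either: the age bands apply to both arms, so propofol adds variance and not bias.

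Four further points:

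- **Stabilisation comes before the block**, so induction hypotension should have settled by then. This is fair as a safeguard. It does not supply a number from which a later fall can be measured.
- **The size can be overstated.** A change score from the pre-induction baseline would have SE 0.365 × √(2(1 − 0.25)) = 0.45 SD, which makes a striking contrast with 0.28. But no change-score analysis is planned, and the existing baseline could equally be used as a covariate. Like for like the contrast is 0.35 against 0.28.
- **Awake and distressed.** That the baseline child is awake, or upset, is an inference from the order of the text. The Protocol says neither and does not mention premedication. The point needs only that the reading precedes induction.
- **Turning differs by arm** (prone for the multifidus block, left lateral for caudal), so a supine reading before turning does not by itself isolate the block. This is largely met by the return to supine straight after injection. That step is written under the CB group only, so the timing of the post-block reading should be made explicit for both arms.

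The choice of analysis baseline could indeed be left to an analysis plan. Whether the value is collected could not.

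**Conclusion.** The point holds as a minor design weakness in a secondary outcome. The schedule records nothing between induction and block. As a result, each block's own haemodynamic effect and individual hypotensive events cannot be attributed to block rather than anaesthesia, and the between-block comparison is less precise than it could be at almost no cost. Under the assumed correlations the loss is about 0.35 against 0.28 SD in the standard error. The correlations are not from the Protocol, and the gain shrinks if the pre-block value predicts the post-block value less well than assumed.

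The point does not show a biased comparison. Nor would the extra reading settle cause completely: there is no arm without a block, isoflurane continues, and surgery follows. It would take induction out of the change being described. The primary outcome and the sample size do not depend on any of this.

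**What to change.** 1. In 2-Intra-operative Settings, add one recorded set of heart rate, MAP and SpO2 after haemodynamic stabilisation, with the child supine, immediately before turning for the block and before the allocation envelope is opened. The last condition keeps the reading free of any influence of allocation.
2. In the intraoperative part of Measurements, list this reading and name it as the baseline: the covariate in the haemodynamic comparison, and the reference for describing falls after the block.
3. State that the reading just after the block is taken once the child is supine again, in both arms.
4. Keep the pre-induction reading as descriptive.

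The cost is one extra line on the record form, from monitors already attached, and a stated moment for opening the envelope. No treatment, dose or clinical rule changes.
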